| Dropout/Removal Criteria | - 1. Participants who do not meet the screening criteria;   2. Participants who are unable to evaluate for efficacy or unable to evaluate safety without receiving 1 dose of the drug;   3. Participants who are treated with chemotherapy, surgical or experimental drugs other than this protocol during the trial;   4. Participant's concurrent use of China Food and Drug Administration (CFDA)-approved modern herbal agents and immunomodulatory agents for the treatment of tumors;   5. Participants who do not follow the dose, method, and course of treatment according to the study protocol. |
| Termination Criteria | Subject must termination the study if the following cases occur (including but certainly not limited to):   - 1. Disease progression (PD) determined according to RECIST 1.1 criteria or considered clinically progressive.   2. Termination of treatment decided by the investigator from the patient's best interests.   3. Occurrence of intolerable adverse reactions or severe adverse events confirmed by the investigator.   4. Patients with poor compliance, using drug amounts outside the range of 80% to 120% of the prescribed dose.   5. Patient withdrawal of informed consent.   6. Initiation of other anti-tumor drug treatments affecting efficacy judgment (such as chemotherapy, targeted therapy, or biologic agents).   7. Unexpected pregnancy. |
| Study Schedule | Estimated date of the start of the study: August 2019  Estimated enrollment date of the last subject: August 2020  Estimated date of the end of the study: August 2021 |
| Study Procedures | TQB2450 plus anlotinib hydrochloride capsules were administered in a 21-day cycle until disease progression or intolerance. |
| Primary effect endpoints | Duration of response (DoR); overall survival (OS); 12-month progression-free survival rate; disease control rate (DCR); objective response rate (ORR) (assessed per RECIST version 1.1 at the following time points: 3 weeks after the first therapy, then every 6 weeks thereafter during therapy.) |
| Primary safety endpoints | Dose-limiting toxicities (DLT); maximum tolerable dose (MTD); vital signs; laboratory index; adverse event (AE); immune-related adverse event (irAE); serious adverse event (SAE) according to NCI CTCAE version 5.0. |

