1.2.3.5 Dose recommendation

Taking into consideration the average weight of the Chinese population, receptor occupancy, probability of immunogenicity, clinical convenience, dosages of similar drugs, efficacy, and safety, a proposed fixed dose of 1200 mg per administration every 3 weeks is recommended for later-stage trials. This dosage will be further validated for safety and efficacy in subsequent trials.

1. Study objective

ALTER-L038 study aims to evaluate the efficacy and safety of the combination including anlotinib and TQB2450 in EGFR-positive advanced NSCLC patients who failed prior EGFR-TKIs therapies.

1. Study design
   1. Overall design

This is a multicenter, open-label, single-arm, phase I/II study aimed at evaluating the efficacy and safety of the combination including anlotinib and TQB2450 in EGFR-positive advanced NSCLC patients who failed prior EGFR-TKIs therapies.

The first stage of the study is a phase I 3+3 dose-escalation study, starting with 8 mg anlotinib in combination with 1200 mg TQB2450 as the initial dose, with three dose levels set at 8 mg/10 mg/12 mg. Phase I study is expected to enroll 18 participants.

The second stage is a multicenter, single-arm phase II study using the MTD determined in the first stage, with an estimated enrollment of 54 participants. This study started in August 2019, with recruitment concluding around August 2020, and the estimated end date is August 2021.

In the absence of withdrawal of consent, intolerable side effects, or a decision by the investigator to be inappropriate for further trial, treatment is continued for each subject until radiographically confirmed disease progression.

- 1. Type of comparison

The phase I study is designed for descriptive statistics without comparative analysis.

The phase II study is a single-arm study using historical controls. The primary efficacy endpoint is PFS. A statistically significant extension in PFS compared to historical controls, reaching a clinically meaningful difference (defined as a PFS extension of ≥4 months when comparing the trial and historical groups, using 30.5 calendar days as a month), would be considered a positive outcome for the study.

- 1. Sample size calculation

Phase I part: Following the 3+3 dose-escalation design, the study anticipates a minimum of 3 and a maximum of 18 participants to be enrolled.

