14. CTCAE grade 3 fatigue, lasting for >7 days
15. CTCAE grade 3 hypertension, hand-foot skin reaction, diarrhea, nausea, and vomiting that are not relieved by symptomatic treatment until the next treatment cycle.
16. CTCAE grade 3 abnormal laboratory examinations that are not relieved by symptomatic treatment until the next treatment cycle.

If one subject experiences toxicity that met the criteria for DLT, the study treatment was interrupted and follow-up was performed as described in the study procedures. Treatment can be discontinued due to any DLT. However, under the investigator and co-sponsor approval, subjects with DLT could receive the next lowest dose level after recovery.

- 1. Efficacy assessment
     1. Primary endpoint
- **Progression-free survival:**

PFS is defined as the time from enrollment to the first time of PD or death from any cause, whichever occurs first.

If the subject did not experience disease progression or death, PFS is defined as the date of the last confirmed progression-free. Subjects who discontinued for reasons other than disease progression (no subsequent tumor imaging assessment) and starting subsequent therapy after the trial were censored at the time of discontinuation or the initiation of subsequent therapy. In cases other than those described above, pre-planned sensitivity analyses will undertake to define PFS based on the date of confirming imaging progression events. New onset other tumor is not considered indicative of PD and is not censored as data.

If the image examination and assessment show PD, the date of PD is not defined as the imaging time of first signs of PD, but the time of definite imaging evidence of PD. If the PD is diagnosed with other clinical examinations, the date of PD is defined as the diagnosis time.

- - 1. Secondary endpoints
- **OS:** OS is defined as the time from enrollment to the date of death due to any cause. For the analysis of OS, data for patients who are alive will be censored for OS at the time of the last follow-up. Data for patients who were lost to follow-up will be censored for OS at the last date they were known to be alive. Censored OS is defined as the time from randomization to censor.
- **1-year PFS rate:** 1-year PFS rate is defined as the percentage of patients who have not progressed or died at 1 year.
- **1-year OS rate:** 1-year OS rate is defined as the percentage of patients who are still alive at 1 year.

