- Full Analysis Set: According to the intention-to-treat (ITT) principle, the efficacy analysis was performed on all cases that received at least one dose of the drug.
- Per-protocol set (PPS): All randomized subjects who received at least 6 weeks of medication, had at least one imaging assessment, meeting the trial protocol, with favorable compliance, did not use prohibited drugs during the trial, and complete CRF. No imputation of missing data. Efficacy analysis was conducted based on both the FAS and PPS populations.
- Safety analysis set: All randomized subjects have received at least one dose of the research drug and have a post-administration safety record were included in the safety analysis set. This data set was used for the safety analysis.
  1. **Statistical Analysis Plans**

All statistical analyses were based on SAS version 9.4 or above. The quantitative variables were listed as mean, standard deviation, median, quartile, minimum and maximum values. Qualitative variables are listed as frequencies and percentages, with two decimal places reserved for percentages. The Kaplan-Meier method was used to analyze time-to-event data.

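### The per-protocol set's 6-week medication rule removes the earliest PFS events and favours the drug, and the success rule in Protocol 3.2 names no analysis set

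*Protocol*

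**What the plan says.** Protocol 8.1 (Analysis datasets) defines the FAS by reference to the intention-to-treat principle: "the efficacy analysis was performed on all cases that received at least one dose of the drug". The PPS is restricted to "All randomized subjects who received at least 6 weeks of medication, had at least one imaging assessment", plus compliance, no prohibited drugs and a complete CRF. The same bullet ends: "Efficacy analysis was conducted based on both the FAS and PPS populations".

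Protocol 3.2 (Type of comparison) states: "The primary efficacy endpoint is PFS". A positive outcome there needs a statistically significant extension over the historical control and also a clinically meaningful one, "defined as a PFS extension of ≥4 months when comparing the trial and historical groups, using 30.5 calendar days as a month". No analysis set is named in 3.2, in the endpoint definition in 6.4, or in the efficacy analysis part of 8.2.

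Three other statements determine who can enter the PPS:
- Endpoint (6.4): "PFS is defined as the time from enrollment to the first time of PD or death from any cause, whichever occurs first".
- Synopsis, termination criteria, first item: "Disease progression (PD) determined according to RECIST 1.1 criteria or considered clinically progressive".
- Synopsis, timing of response assessment: "3 weeks after the first therapy, then every 6 weeks thereafter during therapy".

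**The concern.** Six weeks on medication can be known only after enrolment, and a patient who has a PFS event early cannot reach it. A patient found to have progressed at week 3 stops treatment and leaves the PPS. So does one who progresses clinically or dies before week 6. Everyone who remains carries an opening period in which, by construction, few or no events can occur.

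In a two-arm trial such a rule would act on both arms. Here there is one arm and a fixed 5-month value, so nothing within the trial offsets it. The direction is always favourable. At stake is whether a PPS result could be offered as meeting the 3.2 rule when the result in all dosed patients does not.

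**Working it through.** **Inputs from the protocol.** Median PFS 9 months against a historical 5 months, two-sided α 0.05, power 0.90, 20% loss, 54 patients and 32 events (8.2.1); 12 months of accrual within 24 months in total (3.3); 30.5-day months (3.2).

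**Assumptions not in the protocol.** Exponential PFS; uniform accrual; a one-sample log-rank test at z > 1.96, since no test is named; no random dropout in the simulations; medication stopping at the PFS event; and the 4-month gain read as an observed Kaplan–Meier median of at least 9 months.

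**The plan's own figures.**
- Events: D = (1.960 + 1.282)² / [ln(9/5)]² = 30.4, so 31.
- Event probability at a 9-month median, with λ = ln2/9: 1 − (e^(−12λ) − e^(−24λ))/(12λ) = 0.741.
- Patients: 30.4/0.741 = 41.04, so 42; 42/0.8 = 52.5, so 53 (stated 54).
- Expected events: 54 × 0.8 × 0.741 = 32.0 (stated 32).

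The exponential model thus reproduces the plan closely enough to use for the rest.

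**Who is excluded.** Week 3 = 21/30.5 = 0.69 months; week 6 = 42/30.5 = 1.38 months. The share with an event by time w at median M is 1 − exp(−ln2 × w/M).

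| True median | Events by week 3 | Events before week 6 |
|---|---|---|
| 9 months | 5.2%, 2.8 of 54 | 10.1%, 5.4 of 54 |
| 5 months | 9.1%, 4.9 of 54 | 17.4%, 9.4 of 54 |

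**Shift in the median.** For an exponential time, the median among those event-free at w is M + w. With week-3 events removed, 5 becomes 5.69 and 9 becomes 9.69. With all events before week 6 removed, they become 6.38 and 10.38. The gain is 0.7 to 1.4 months against the 4-month margin.

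**Effect on the decision.** Simulated trials of 54 patients (5,000 to 20,000 per setting, so the percentages are good to about one point):

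| True median and criterion | All dosed | Week-3 events removed | All events before week 6 removed |
|---|---|---|---|
| 5 months, significance only | about 2% | 6–9% | 18–23% |
| 5 months, full 3.2 rule | about 0.1% or less | about 0.3% | about 2% |
| 7 months, full 3.2 rule | about 11% | about 17% | about 33% |
| 8 months, full 3.2 rule | about 31% | about 41% | about 58% |

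The ranges in the first row cover two standard variance forms of the test and separate runs.

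**Progression seen only at scheduled scans (weeks 3, 9, 15 and so on).** All dosed against PPS:
- True median 5 months: significance alone 6.2% against 18.3%; full rule 0.1% against 0.3%.
- True median 7 months: full rule 11.3% against 17.9%.
- True median 8 months: full rule 33.5% against 42.3%.

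**The case against.** **The null error rate.** A reader might infer from the 18–23% that the trial's false-positive rate rises to that level. The protocol does not support this. Section 3.2 also demands a 4-month gain, and with both conditions false success at a true 5-month median is about 2% even in the worst case. This objection stands.

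**The week-6 column is an upper bound.** No scan is scheduled between weeks 3 and 9, so events in weeks 3 to 6 enter only as deaths, clinical progression or unplanned imaging. Scheduled scans alone exclude 5–9% of patients. This also stands.

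**The FAS looks primary, and ranking belongs in the SAP.** The FAS carries the intention-to-treat label and keeps every early event among dosed patients. Reporting both sets is ordinary practice, and the order may be fixed in an SAP not at hand. A reader might infer that the PPS decides, or may decide, the trial; no sentence says so. Equally, none ties the success decision to the FAS, although the protocol itself sets both the success rule and the use of both sets. The PPS membership rule is fixed in the protocol and is badly drawn whichever set ranks first.

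**The control.** A reader might assume that the 5-month value came from data without similar selection. The protocol gives only a regimen and a value, so this cannot be verified.

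**Conclusion.** The point holds in limited form. The PPS rule selects on the primary endpoint and biases the PPS result for PFS towards the drug. It removes about 3 to 5 patients if only week-3 events count, and about 5 to 9 if all events before week 6 count, at true medians of 9 and 5 months respectively.

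The bias does not make an ineffective regimen likely to succeed under the full 3.2 rule. It matters for a regimen better than the control but short of the target: at true medians of 7 and 8 months it raises the chance of meeting the rule by about 6 to 22 and 10 to 27 percentage points (17 − 11 and 33 − 11; 41 − 31 and 58 − 31).

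The sizes rest on the assumptions listed above. The direction within the trial arm needs only that medication stops at or soon after the event, as the termination criteria require for progression.

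**What to change.** In 8.1, reword the PPS exposure condition to at least 6 weeks of study treatment, or treatment until progression or death if that comes earlier. Count early progression or death as an evaluable outcome, so that a patient who dies before the first scan is not lost through the imaging condition. State in 8.1 or 3.2 that the success decision rests on the FAS and that the PPS analysis is supportive.

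Replacing the word randomized with enrolled in the PPS and safety set definitions is a clerical correction for this single-arm trial and has no numerical effect.

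The change is to wording only: sample size, visits and the FAS analysis stay as they are. The one downside is a slightly less favourable PPS figure.

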**8.2.1 Sample size**

Phase I: Following the 3+3 principle of dose adjustment, a minimum of 3 and a maximum of 18 patients were expected to be enrolled.

Phase Ⅱ: The mPFS of TQB2450 plus anlotinib hydrochloride capsules was estimated to be 9 months, and the historical control group carboplatin combined with pemetrexed was set as 5 months. The two-sided test level α was 0.05, and the power level was 0.90. It was calculated that 54 subjects would need to be enrolled (considering that the loss to follow-up rate should be controlled at 20%). The study was expected to last 24 months, including 12 months after enrollment. At the end of the study, 32 end-point events were expected to have occurred.

**8.2.2 Distribution of subjects**

The enrollment and completion of the subjects and the reasons for early withdrawal were summarized. The situation of the population in each analysis set was summarized, and the list of subjects' early withdrawal and protocol deviation was listed.

**8.2.3 Demographic characteristics and baseline analyses**

The demographic and baseline characteristics of the subjects (ECOG score, smoking history, etc.) were descriptively analyzed. The mean, standard deviation, median, quartile, minimum and maximum values were listed for quantitative variables, and frequency and percentage were listed for qualitative variables. The demographic and baseline characteristics of the subjects were listed.

**8.2.4 Tumor treatment and concomitant disease treatment history**

Frequency and percentage were used to describe the treatment history of tumor and comorbidities.

**8.2.5 Safety analyses**

Safety analysis includes AEs/adverse reactions, serious AEs/adverse reactions, laboratory tests, vital signs, physical examination, ECOG score, 12-lead electrocardiogram.

- - - 1. **AEs**

Medical coding of adverse events/adverse reactions/immune-related adverse events was performed with the use of MedDRA 21.0. The occurrence of adverse events/adverse reactions/immune-related adverse events, serious adverse events/adverse reactions/immune-related adverse events, adverse events/adverse reactions/immune-related adverse events leading to withdrawal, and adverse events/adverse reactions/immune-related adverse events leading to death were summarized, the number and times of occurrence were listed, and the incidence was calculated. The incidence of adverse events/adverse reactions/immune-related adverse events and serious adverse events/adverse reactions were summarized according to system organ classification (SOC) and preferred terminology (PT), and the number and incidence of adverse events/adverse reactions were listed. The association and toxicity grade of AEs/AEs (NCI CTCAE v5.0) were summarized according to SOC and PT, and the number and incidence of AEs/AEs were listed. The list describes the details of the occurrence of each adverse event/adverse reaction for each subject.

- - - 1. **Laboratory tests**

The laboratory tests were classified according to clinical significance, namely normal, abnormal without clinical significance, abnormal with clinical significance or normal and abnormal. The laboratory tests were summarized descriptively by frequency and percentage using cross-classification table.

Lists describe occurrences of normal before treatment but abnormal after treatment, as well as subjects who were abnormal before treatment but worsened after treatment. The mean, standard deviation, median, quartile, minimum and maximum values of routine blood test, blood biochemistry, four coagulation tests, thyroid function, lipase and amylase were listed. The measured values and changes before and after treatment were described. Paired *t* tests were performed when necessary.

Describe the proportion of subjects with abnormal changes who have “abnormal clinical significance”, in which the investigator judges whether the abnormality has clinical significance.

| Type | Tests |
| --- | --- |
| Hemanalysis | WBC, ANC, LYM, RBC, Hb, PLT |
| Urinalysis | urine RBC, urine WBC, proteinuria, glucose in urine (proteinuria ≥ 2+, additional 24-h urine protein quantification is required within 1 week) |
| Stool tests | leukocyte, RBC, occult blood |
| Blood biochemistry | ALT, AST, GGT, ALP, LDH, TP, ALB, TBIL, DBIL, GLU, BUN/Urea, Cr, K^+^, Na^+^, Cl^-^, Ca^2+^, Mg^2+^, P, TC, TG, HDL, LDL |
| Six coagulation tests | INR, APTT, PT, FIB, TT, D-D dimer |
| Lipase | lipase |
| Amylase | amylase |
| Tumor marker | carcinoembryonic antigen |
| Pregnancy text | human chorionic gonadotophin |
| Epidemiological | HbsAgn (Additional HBV DNA if positive), HBsAb, HBeAg, HBeAb, HBcAb, Anti-HCV, HIV |

- - - 1. **Physical examination**

The physical examination was classified according to normal and abnormal, and the cross-classification table was used. Frequency and percentage were used to summarize the physical examination descriptively.

- - - 1. **Vital signs**

Means, standard deviations, medians, quartiles, and minimum and maximum values will be listed for vital signs, describing the measurements and changes before and after treatment. Paired *t* tests were performed when necessary.

- - - 1. **12-lead electrocardiogram**

The 12-lead electrocardiogram was classified according to clinical significance, namely normal, abnormal without clinical significance, abnormal with clinical significance or normal and abnormal. The 12-lead electrocardiogram was summarized descriptively by frequency and percentage using cross-classification table.

- - - 1. **Concomitant medications**

The WHODrug was used to code the combined drugs, and the use of combined drugs during the study period and the frequency of each drug were summarized. The details of the combined drugs are listed.

- - 1. **Efficacy analysis**
       1. **Analysis of primary efficacy endpoints**

PFS is defined as the time from enrollment to the first time of disease progression or death from any cause, whichever occurs first.

If the subject did not experience disease progression or death, PFS is defined as the date of the last confirmed progression-free. Subjects who discontinued for reasons other than disease progression (no subsequent tumor imaging assessment) and starting subsequent therapy after the trial were censored at the time of discontinuation or the initiation of subsequent therapy. In cases other than those described above, pre-planned sensitivity analyses will undertake to define PFS based on the date of confirming imaging progression events. New onset other tumor is not considered indicative of PD and is not censored as data.

If the image examination and assessment show PD, the date of PD is not defined as the imaging time of first signs of PD, but the time of definite imaging evidence of PD. If the PD is diagnosed with other clinical examinations, the date of PD is defined as the diagnosis time.

- - - 1. **Analysis of secondary efficacy endpoints**

OS is defined as the time from enrollment to the date of death due to any cause. For the analysis of OS, data for patients who are alive will be censored for OS at the time of the last follow-up. Data for patients who were lost to follow-up will be censored for OS at the last date they were known to be alive. Censored OS is defined as the time from randomization to censor.

One-year progression-free rate is defined as the probability of patients experiencing the endpoint events of disease progression from enrollment to one year. Endpoint events include disease progression, death, and withdrawal due to intolerance.

One-year survival rate is defined as the probability of patients experiencing the endpoint event of death from enrollment to one year.

DOR is defined as the time from the date of CP and PR until the date of disease progression. Subjects who discontinued for reasons other than disease progression (no subsequent tumor imaging assessment) and starting subsequent therapy after the trial were censored at the time of discontinuation or the initiation of subsequent therapy. New onset other tumor is not considered indicative of PD and is not censored as data.

DCR is defined as the percentage of subjects with PR, CR, or SD lasting for ≥4 weeks.

ORR is defined as the percentage of subjects with confirmed tumor volume reduction to pre-specified values and lasting for ≥4 weeks, including subjects with a PR or CR. Objective responses are assessed per RECIST v1.1. Subjects must have at least one measurable lesion at baseline. The response was classified as CR, PR, SD, and PD according to RECIST v1.1.

For PFS, OS, and DOR, Kaplan-Meier was used to estimate median survival and draw survival curves, and the 1-year disease progression rate and 1-year survival rate were also estimated. For ORR and DCR, the Clopper-pearson method was used to estimate 95% confidence intervals.

1. **Project management**
   1. **Information promulgation**

The present study will be registered and publicized in the Chinese Clinical Trial Registry after obtaining ethical approval from the responsible unit of the clinical study.

- 1. **GCP and ethics committee review and approval**

This clinical trial will be conducted in accordance with the Declaration of Helsinki (2013), the GCP promulgated by the NMPA and related regulations. The investigator will not begin any study subject activities until approval from the Clinical Research Ethics Committee of the Clinical Trial Team leader. Any modifications of the protocol during the clinical study should be declared and filed to the Ethics Committee.

Clinical investigators will follow all applicable regulations to protect subjects. The informed consent document used in the trials must be reviewed by the sponsor, approved by the ethics committee, and available for inspection.

- 1. **Informed consent**

Clinical investigators must make it clear to subjects that participation in clinical trials is voluntary, and they are completely free to refuse to enter the study or to withdraw from it at any time, for any reason, without incurring any penalty or withholding of treatment on the part of the investigator, and the rights and welfare of the subjects will be protected. The investigator must make the subject aware that participants in the trial and their personal information will be strictly maintained confidential. It is the responsibility of the investigator to provide an adequate explanation in understandable language of the aims, importance, anticipated benefits, potential hazards, consequences of the study, other available treatment options, and the rights and obligations of the subject under the Declaration of Helsinki. Adequate time will be provided to ensure that the subject has time to consider and discuss participation in the protocol and sign the informed consent.

Before participants enrolled in this study to perform any of the procedures required by the protocol, subjects must:

- Be informed of all contents of the study and all the contents and terms of the informed consent form.
- Be provided adequate time to consider and discuss participation in the protocol and sign the informed consent whether to participate in the study.
- Voluntary consent to participate in the study.
- Personally (or their legally authorized representative) signed and dated the informed consent form approved by the Ethics Committee.

If there are any updates or amendments to the informed consent form during the trial, written informed consent should be obtained using the updated/amended informed consent form for subjects continuing in the trial.

- 1. **Protocol** **modification**

Protocol modifications to ongoing studies if necessary must be submitted to the Ethics Committee again for approval before implementation. Approval of the ethics committee and the sponsor must be obtained before any changes can be implemented, except for changes necessary to eliminate an immediate hazard to trial subjects. Changes to eliminate an immediate hazard to trial subjects can be performed immediately, but the change must be documented in a protocol modification, reported to the ethics committee, and submitted to the appropriate regulatory agency within the required deadline.

If protocol modifications involve important new information of the investigated drug, the informed consent must be revised and sent to the ethics committee for approval, and then the subject's consent must be obtained again.

- 1. **Protocol deviation**

The investigator should document and account for all protocol deviations, and report all protocol deviations that may affect subject safety and data integrity to the ethics committee and the sponsor in a timely manner.

- 1. **Retention of document**

The investigator must maintain adequate and accurate records to enable the conduct of the study to be fully documented, including but not limited to the study protocol, study protocol modification documents, informed consent forms, and ethics committee and government approval documents.

- 1. **Study discontinuation**

1. Serious safety issue is identified by the investigators;

2. Efficacy too poor to continue the trial;

3. Major mistakes in the protocol make it difficult to evaluate drug effects;

4. Discontinuation of the study at the request of the administrative department.

Full discontinuation of the trial can be temporary or permanent and the discontinuation of the test should retain all test records for review.

- 1. **End of study**

Based on the statistical analysis of the trial, the investigation director summarizes the results objectively and in detail, and actively completes the end-of-trial study report to meet the unified regulatory requirements for the clinical review of new drugs. Each participating unit completes the report of the sub-center.

- 1. **Quality control and quality assurance**

To ensure the quality of the trial, the clinical study program will be discussed and established by the sponsor and the investigator before the trial formally begins. GCP training will be conducted for relevant investigators participating in the trial. Each research center must manage study drugs in accordance with the protocol and SOPs, including receipt, storage, distribution, retrieval, and destruction (if applicable).

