**(3) Observation and recording of AEs**

Any medical events that occurred from starting treatment until 28 days after the end of the study drug or the initiation of other anti-tumor therapy, regardless of its causality to study drugs, are considered to be an AE.

If laboratory abnormalities were part of a syndrome, the syndrome or diagnostic finding (e.g., anemia) rather than the laboratory finding (i.e., decreased hemoglobin) will be recorded.

The following information about AEs should be recorded, including time of AE occurrence (starting time) and recovery time (ending time), severity, the causality of AEs to study drugs, follow-up, outcomes, and managements.

AEs are followed-up until the disease is stable, normalized, and returned to baseline.

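### The laboratory frequency table in 8.2.5 is not by CTCAE grade, so worsening from an abnormal baseline is counted by grade only if the investigator reports it as an adverse event

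*Protocol*

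**What the plan says.** The synopsis lists the primary safety endpoints as DLT, MTD and then "vital signs; laboratory index; adverse event (AE); immune-related adverse event (irAE); serious adverse event (SAE) according to NCI CTCAE version 5.0".

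Under Laboratory tests, section 8.2.5 of the protocol sets the scale: "The laboratory tests were classified according to clinical significance, namely normal, abnormal without clinical significance, abnormal with clinical significance", or, as an alternative, just the two levels normal and abnormal. It also sets the form of the output: "The laboratory tests were summarized descriptively by frequency and percentage using cross-classification table". Clinical significance is a matter of opinion, "in which the investigator judges whether the abnormality has clinical significance".

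The same section plans three further outputs that bear on laboratory toxicity:

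- a listing of subjects normal before and abnormal after treatment, "as well as subjects who were abnormal before treatment but worsened after treatment";
- means, standard deviations, medians, quartiles and extremes of measured values and of changes from before treatment;
- adverse event tables by CTCAE v5.0 grade within system organ class and preferred term.

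Section 6.5 applies CTCAE v5.0 to the severity of adverse events. Its paragraph on pre-treatment events leaves it to the investigator whether a pre-existing abnormality that worsens on treatment is an adverse event.

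**The concern.** Elsewhere the protocol handles laboratory toxicity by CTCAE grade or multiple of ULN. The one planned laboratory frequency table uses a different scale, and that scale does not measure severity. A patient who enters with an abnormal value can worsen a long way without leaving the abnormal category.

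The stake is a descriptive safety result. For a new combination in an open-label, single-arm trial, a reader will want to know what proportion of patients reached grade 3 or 4 on each laboratory parameter. As planned, that proportion comes only from adverse event reports, which depend on unblinded judgement, although the values themselves are measured at scheduled visits.

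**Working it through.** The plan states no figure on this point, so there is nothing to recompute. The check sets the sections side by side.

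**1. Scale used where laboratory toxicity drives a decision.** Tables 5.5-2 to 5.5-5 (platelets, neutrophils, liver function, proteinuria) are organised by grade. Table 5.5-10 defines hepatitis by multiples of ULN and places ALT or AST of 5×ULN or more in grade 3 or worse. The DLT definition in section 6.3 uses CTCAE grades for bilirubin, ALT/AST, neutrophils, platelets and other laboratory results, but it covers the first 21 days.

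**2. Scale used in the laboratory frequency table.** Section 8.2.5 allows three levels (normal, abnormal without clinical significance, abnormal with clinical significance) or two (normal, abnormal). It names no grade and does not say which version applies.

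**3. Can patients enter with abnormal values?** Yes. Section 4.2 allows ALT, AST, INR and APTT up to 1.5×ULN, so any value above ULN and up to that limit is abnormal at baseline and still eligible.

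**4. What each version does with worsening from an abnormal baseline.** Take ALT of 1.4×ULN at entry (eligible, since 1.4 ≤ 1.5) rising to 6×ULN. That is a factor of 6 / 1.4 ≈ 4.3, and it passes the 5×ULN line in Table 5.5-10.

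| Baseline category | Two-level table | Three-level table |
| --- | --- | --- |
| Abnormal, not clinically significant | stays abnormal → abnormal | moves only if the investigator now judges it significant; grade not shown |
| Abnormal, clinically significant | stays abnormal → abnormal | stays in the same cell at any value |

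In the two-level table, a patient moving from 1.4×ULN to 1.5×ULN falls in the same cell as one moving from 1.4×ULN to 6×ULN.

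**5. Do the other outputs supply a rate by grade?**

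- The listing identifies the patients who worsened, but it gives no count and no grade.
- Summaries of measured values and changes describe the distribution. The maximum shows the most extreme value, but none of them gives the number of patients per grade.
- The adverse event tables do count by CTCAE grade. They contain what the investigator records as an adverse event, and for a pre-treatment abnormality that worsens, section 6.5 makes this a judgement. Section 6.5 also says: "If laboratory abnormalities were part of a syndrome, the syndrome or diagnostic finding (e.g., anemia) rather than the laboratory finding" is to be recorded. The event is then graded under the diagnosis and is not lost, but it cannot be read as a count for the laboratory parameter.

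**6. The synopsis.** The CTCAE phrase closes the list, directly after SAE. It may govern the whole list or only the AE, irAE and SAE items. MTD is a dose and cannot be graded, so the phrase cannot sensibly cover every item, and section 6.5 applies CTCAE to adverse event severity.

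**The case against.** The strongest reply is that a grade-shift table is ordinary SAP content, that the SAP is not shown, and that nothing in 8.2.5 forbids such a table. This stands in part: an SAP could add it without contradicting the protocol. But the protocol is not silent here. It chooses the scale, the form of the table and the person who judges, and a scale that has been chosen can be reviewed.

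The second reply is that a marked rise would rarely go unreported. Table 5.5-4 calls for delay and dose reduction at grade 3-4, section 5.5 requires the reason to be documented in the medical record and EDC, and adverse events leading to withdrawal are summarised. That makes severe cases less likely to be missed. It does not turn the count into one based on measured values.

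Four stronger readings are tempting, and the documents do not support them:

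- **Laboratory results are analysed only by clinical significance.** They are not: 8.2.5 also plans the listing of patients who worsened, the quantitative summaries and a plain normal/abnormal option.
- **Grade 3-4 laboratory toxicity is never counted.** It is counted when it is recorded as an adverse event.
- **Every patient abnormal at baseline is affected.** In the three-level table, a patient whose baseline abnormality was not clinically significant can still change cell.
- **The synopsis and 8.2.5 contradict each other.** They do so only if the CTCAE phrase covers the laboratory index. If it covers only adverse events, the two agree.

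**Conclusion.** The point holds in a limited form. The laboratory frequency table is on a scale that does not show severity. For patients with abnormal baselines, no planned output gives a rate by grade from the measured values; the graded count depends on adverse event reporting by unblinded investigators. Whether this is also a mismatch with the endpoint depends on how the synopsis is meant, which the text leaves open.

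The size cannot be stated. The documents do not give the share of patients abnormal at baseline, or say whether the two-level or three-level table will be used. The effect is confined to descriptive safety reporting: the DLT criteria already use CTCAE laboratory grades, and the PFS analysis, alpha and sample size are untouched. The conclusion assumes that no SAP adds a graded laboratory table; if one does, only the wording of the synopsis remains to be settled. This is a cheap improvement, not a flaw that threatens the trial's conclusions.

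**What to change.** In 8.2.5, add for each gradable laboratory parameter a table of baseline versus worst post-baseline CTCAE v5.0 grade. Derive the grades by program from the recorded values and normal ranges, and include both scheduled and unscheduled tests. Keep the clinical-significance table as supportive, alongside the listings and summaries of change.

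In the synopsis, state whether CTCAE v5.0 applies to the laboratory index or only to AE, irAE and SAE.

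The cost is the programming of one standard table from data already collected, and a one-phrase edit. No extra tests or visits are needed.
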